## Statistical analysis

Descriptive statistics will be used to describe baseline characteristics of the treatment groups. The comparison of between group difference in both primary and secondary outcome variables will be performed according to the intention to treat principle.

Analysis of variance will be applied to evaluate the difference between groups in the change of primary outcome measure (SPADI) between the baseline and 24 weeks follow-up, adjusting for demographic and medical factors such as age, sex, education, sick leave, duration of symptoms, calcification in the rotator cuff, dominant arm affected, bilateral shoulder pain, drug use, emotional distress and compliance to the rESWT treatment. Secondary outcome measures will be assessed with the same approach in separate models. Cox regression will be used to analyse the secondary outcome of return to work at 1 year follow-up.

Finally, mixed model will be applied to explore the variations of the mean SPADI from baseline through the 1-year follow-up within and between patients (between the intervention groups) simultaneously. The effects of demographic and clinical factors on the change of SPADI will also be explored. Number needed to treat will be calculated according to Guyatt et al [30]. Bonferroni correction will be used to correct for multiple testing of secondary outcome.

To deal with missing values of the important analytic variables multiple imputation will be carried out. Estimations from the imputed data will be compared with the estimation from the data with complete values.

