Musculoskeletal ultrasound might be an important supplement to the clinical examination [4]. Ultrasound can reliably detect calcification, partial and full-thickness tears, bursitis and tendinopathy [15]. Ultrasound examination may be particularly valuable when considering rESWT because rESWT would be expected to be most useful in case of calcification. With respect to routine radiological examination (MRI and ultrasound), a recent study found that structural changes in the rotator cuff and subacromial bursa did not predict short-term outcome after corticosteroid injection therapy [16].

Physiotherapy treatment for subacromial shoulder pain often is a combination of rESWT and exercise therapy. In a recent randomised single blind study the short-term effect of supervised exercises was significantly better than the effect of rESWT on subacromial shoulder pain, but both groups improved [17]. A clinical trial on achilles tendinopathy showed that rESWT significantly improved the effectiveness of eccentric training [18]. However, these studies did not comprise a sham rESWT study arm.

Additionally, previous studies have reported that the prognosis of subacromial shoulder pain is affected by education, work status, polymedication and high baseline pain and disability [16, 19, 20].

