## Sample size

A previous study indicates an expected standard deviation (SD) of 20 points [17]. To detect a difference in SPADI on 10 points between the groups with a statistical power of 80 % and a significance level of 0.05 we need 50 persons in each group. We have planned to include 144 persons to account for drop out and possibly higher variance.

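### The primary ANOVA of SPADI change does not name baseline SPADI among its covariates; making it mandatory would be a free gain in precision

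*Protocol article*

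**What the plan says.** The Statistical analysis section of the protocol article gives the endpoint and model together. The method is an analysis of variance, and its target is the "difference between groups in the change of primary outcome measure (SPADI) between the baseline and 24 weeks follow-up". The adjustment set comes next: "adjusting for demographic and medical factors such as age, sex, education, sick leave, duration of symptoms, calcification in the rotator cuff", then "dominant arm affected, bilateral shoulder pain, drug use, emotional distress and compliance to the rESWT treatment". That makes eleven named factors. They are introduced by *such as*, so the list is illustrative, and baseline SPADI is not one of them. Continuous secondary outcomes are to be analysed in the same way in separate models.

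The Background reports earlier work showing that "the prognosis of subacromial shoulder pain is affected by education, work status, polymedication and high baseline pain and disability". The Outcome measurements and assessment section places the primary and secondary outcome measures in the baseline questionnaire, and the Participants section uses a minimum SPADI for entry. The Randomisation and blinding section describes 1:1 allocation in blocks of 20 and mentions no stratification by SPADI.

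A mixed model of SPADI from baseline through one year is also planned, but as an exploratory analysis. It does not replace the 24-week comparison.

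**The concern.** The protocol does not carry its own prognostic reasoning through to its primary model. Of the four prognostic factors in the Background, three have close counterparts in the covariate list: education, sick leave for work status, and drug use for polymedication. The fourth, baseline pain and disability, is what SPADI measures, and it has none.

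Subtracting the baseline is not the same as adjusting for it. A change score fixes the slope of follow-up on baseline at 1, whereas the actual slope is usually lower. Two consequences follow. The treatment estimate has a larger variance than it needs. And if one arm starts worse by chance, it will tend to show more improvement through regression to the mean, which the change score credits to treatment.

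Precision matters here because the Discussion says that finding no difference would count against recommending rESWT. Avoidable imprecision makes a missed effect more likely.

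**Working it through.** **Inputs from the protocol article (Sample size).** "A previous study indicates an expected standard deviation (SD) of 20 points"; a target of 10 points ("To detect a difference in SPADI on 10 points between the groups"); power 80 %; significance level 0.05; 50 needed per group; 144 planned, so 72 per group. The section does not say whether the level is one- or two-sided, or whether SD 20 refers to the score or to its change.

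**Assumed, because the document gives no value.** The correlation r between baseline and 24-week SPADI, shown at 0.3, 0.5 and 0.7; the SDs at the two times; no dropout; no other covariates. Power uses the normal approximation.

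**1. The plan's own figure.** n per group = 2 × SD² × (z_α + z_power)² / difference².
- One-sided 0.05: 2 × 400 × (1.645 + 0.842)² / 100 = 49.5, so 50, as stated.
- Two-sided 0.05: 2 × 400 × (1.960 + 0.842)² / 100 = 62.8, so 63.

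The sidedness question is separate and does not affect this point. Two-sided 0.05 is used below.

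**2. Variance of the two analyses.** Let b be the baseline SD and f the follow-up SD.
- Change score: b² + f² − 2rbf
- ANCOVA: f²(1 − r²)
- Difference: (b − rf)², which is never negative

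Apart from the degree of freedom spent on the covariate, ANCOVA is therefore never the less precise. With b = f, the ratio of ANCOVA to change-score variance is (1 − r²) / [2(1 − r)] = (1 + r)/2.

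| r | Ratio, equal SDs | Ratio, b = 15 and f = 20 |
|---|---|---|
| 0.3 | 0.65 | 364/445 = 0.82 |
| 0.5 | 0.75 | 300/325 = 0.92 |
| 0.7 | 0.85 | 204/205 = 0.995 |

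The last column is an illustration. Because a SPADI below 20 bars entry, the baseline distribution is cut off while the follow-up distribution is not, so a smaller baseline SD is plausible.

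**3. Power at 72 per group, SD 20 read as the raw-score SD, equal SDs.** The standard error is SD × √(2/72) = SD/6.

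| r | SD of change | SD after ANCOVA | Power, change | Power, ANCOVA |
|---|---|---|---|---|
| 0.3 | 23.7 | 19.1 | 71.8 % | 88.2 % |
| 0.5 | 20.0 | 17.3 | 85.1 % | 93.4 % |
| 0.7 | 15.5 | 14.3 | 97.2 % | 98.7 % |

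If SD 20 is instead the SD of the change, the change score has 85.1 % power whatever r is, and ANCOVA has 96.1 %, 93.4 % and 90.2 % at r = 0.3, 0.5 and 0.7.

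**4. Chance imbalance.** With baseline SD 20 (assumed), the standard error of the baseline difference between arms is 20 × √(2/72) = 3.3 points, so a 5-point difference is plausible. With equal SDs, a baseline difference D shifts the change-score estimate by (r − 1) × D. For D = 5 the shift is −3.5, −2.5 and −1.5 points at r = 0.3, 0.5 and 0.7. At r = 0.5 that is a quarter of the 10-point target.

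**The case against.** The strongest objection is that the list is open. A reader might infer that the protocol excludes baseline SPADI, and the text does not support that: *such as* leaves room for it, and an analysis plan that is not shown might include it. That limits the point but does not remove it. The article states endpoint, model and eleven covariates without deferring the choice elsewhere, and an open list does not commit anyone to the baseline value.

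Three other stronger readings also fail.
- *The primary analysis is biased.* It is not. Randomisation keeps the change-score estimate unbiased on average, and its standard error already allows for chance imbalance. The shifts in step 4 are conditional on an imbalance having occurred.
- *The trial is underpowered as planned.* The documents do not show this. At 72 per group, the change score has about 85 % power at r = 0.5, or at any r if SD 20 is the SD of the change. Power below 80 % requires a lower r under the raw-score reading, dropout at a rate the protocol does not give, or a larger SD.
- *Baseline SPADI is the strongest predictor available.* The Background lists baseline severity beside three other factors and does not rank them.

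The size of the gain is also open to challenge, and that challenge stands. With SDs of 15 and 20 most of it disappears at the higher correlations. The comparison ignores the planned covariates, and emotional distress, drug use and sick leave may recover part of the gain. The mixed model, being exploratory, does not answer the concern.

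**Conclusion.** The point holds as one of precision and of a model not firmly specified; it is not an error of validity. Baseline SPADI is not named in an otherwise detailed covariate list, although the protocol itself treats baseline severity as prognostic and collects the value.

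Under equal SDs and no other covariates, adding it removes 35 %, 25 % or 15 % of the variance of the treatment estimate at r = 0.3, 0.5 or 0.7. With the illustrative SDs of 15 and 20, it removes about 18 %, 8 % or less than 1 %. The gain in power depends on r, on which SD the 20 points describe, and on dropout, none of which the document settles. The direction depends on none of them: in a trial of this size the adjusted analysis is essentially never less precise, and it removes the estimate's dependence on chance baseline differences in SPADI.

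**What to change.** State that the primary model is an ANCOVA of 24-week SPADI, or equivalently of its change, on treatment group with baseline SPADI as a mandatory covariate. Once baseline is in the model, the two outcome forms give the same treatment estimate. For each continuous secondary outcome (pain at rest, pain on activity, the function items, EQ-5D, EQ-VAS), include that outcome's own baseline value in its model.

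The cost is one phrase in the analysis section, to be settled before unblinding. No new data are needed, since the primary and secondary measures are already in the baseline questionnaire, and the sample size need not change.

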The first 4 weeks, the patients receive rESWT or sham once a week in addition to the exercises. The rESWT or sham treatment (SwissDolorClast/EMS) is given by one of two physiotherapists who both went through an application course and training before the study started. The rESWT/sham is given on one to three tendons (supraspinatus, infraspinatus and/or subscapularis), depending on which tendons are painful at isometric tests. Two thousand impulses of shock waves are applied to each painful tendon, with a pressure between 1,5 and 3 bar (depending on what the patient tolerates). We use a power handpiece, which provides an energy of 0,01 – 0,35 mJ/mm2. This handpiece was chosen after advice from the producer (Enimed/SwissDolorClast), physiotherapists with experience in rESWT, and a previous systematic review concluding that future research on rotator cuff tendinosis should focus on high-energy shock wave [27].

The sham rESWT is administered in the exact same way as the rESWT. The sham handpiece is similar to the real handpiece in design, shape and sound, and vibrates exactly like the real handpiece, but no real shock waves are conducted.

Compliance to the treatment is recorded.

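### The intention-to-treat model for SPADI adjusts for compliance with rESWT, a post-randomisation variable, which can bias the estimated effect of assignment

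*Protocol article*

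**What the plan says.** The Statistical analysis section states that the between-group comparison of primary and secondary outcomes "will be performed according to the intention to treat principle". The next paragraph defines the primary analysis as an analysis of variance of the change in SPADI from baseline to 24 weeks, "adjusting for demographic and medical factors such as age, sex, education, sick leave, duration of symptoms" and further items, ending with "drug use, emotional distress and compliance to the rESWT treatment". For the other outcomes it adds: "Secondary outcome measures will be assessed with the same approach in separate models". Return to work at 1 year is assigned to Cox regression, for which no covariates are stated.

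The timing of compliance follows from the Interventions section: "The first 4 weeks, the patients receive rESWT or sham once a week in addition to the exercises". The same section closes with "Compliance to the treatment is recorded", without a definition. No other section moves compliance to a per-protocol, sensitivity or exploratory analysis, and no other model is given for the primary comparison.

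**The concern.** Compliance is the one variable in the list that cannot be known at randomisation. Outcome measurements and assessment places age, sex, education, symptom duration, drug use, sick leave and emotional distress in the baseline questionnaire. Compliance is a result of what happens once treatment starts, although the list presents it as a demographic or medical factor.

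The arm may affect it. According to Interventions, the active handpiece delivers shock waves at a pressure that depends on tolerance, while the sham handpiece delivers none. If the active treatment is less comfortable, some patients may miss sessions that they would have attended on sham. Those who still attend fully on rESWT are then a more selected group, perhaps less sensitive to pain or more motivated, than full attenders on sham. A model that holds compliance fixed compares these two differently selected groups. If the same traits also influence SPADI change, the group coefficient absorbs part of their effect.

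At stake is the trial's main result. If attendance is lower on rESWT and good attenders improve more, the bias favours rESWT, and an inactive treatment can appear to work.

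**Working it through.** **Inputs from the protocol article (Sample size):** SD 20 points, target difference 10 points, 144 patients planned. With 1:1 allocation (Randomisation and blinding) this is 72 per group. The article gives no compliance rate, so there is no figure of its own to reproduce here.

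**Assumptions (not in the article):** true effect 0; 95 % full compliance on sham; a latent patient trait correlated 0.5 with a good outcome and 0.6 with compliance (0.9 for strong selection), the same in both arms. Lower SPADI is better, so a negative bias favours rESWT.

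**Step 1, the bias.** When the true effect is 0, the adjusted group coefficient is approximately

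bias = -(compliance coefficient) x (compliance on rESWT - compliance on sham).

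Example: at 80 % against 95 %, full compliers score about 11 points better, a coefficient of -11. Bias = -(-11) x (0.80 - 0.95) = -1.65, or about -1.7 points. The compliance coefficient is not constant across scenarios, so the other cases come from a large-sample simulation of the same set-up.

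**Step 2, the type I error.** SE = 20 x sqrt(2/72) = 3.33. For a bias b, the two-sided rejection rate is Φ(-1.96 - b/SE) + Φ(-1.96 + b/SE).

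| Full compliance, rESWT vs sham | Bias (correlation 0.6) | Bias (correlation 0.9) |
|---|---|---|
| 95 % vs 95 % | 0 | 0 |
| 90 % vs 95 % | -0.6 | -0.9 |
| 80 % vs 95 % | -1.7 | -2.5 |
| 70 % vs 95 % | -2.6 | -3.9 |

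| Size of bias (points) | Two-sided type I error |
|---|---|
| 0 | 5.0 % |
| 0.6 | 5.4 % |
| 0.9 | 5.8 % |
| 1.5 | 7.3 % |
| 2.5 | 11.7 % |
| 3.9 | 21.6 % |

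Without compliance in the model, the estimate was about 0 throughout.

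**Step 3, a check at trial size.** A separate simulation used 144 patients, SD 20, compliance counted as 0 to 4 sessions and 4,000 runs. An unmeasured factor was assumed to change the log-odds of attending by 0.8 per SD and SPADI change by 10 points per SD.

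- Equal attendance, compliance in the model: mean estimate 0.0, type I error 5.1 %.
- Attendance lower on rESWT by 0.5 on the log-odds scale (for an average patient, 1/(1 + e^-1.5) = 82 % per session on sham against 1/(1 + e^-1.0) = 73 % on rESWT): bias -1.8 points, type I error 8.5 %. With a true effect of -10 the mean estimate was -11.8.
- Without compliance in the model: type I error 4.6-5.3 % and no bias.

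Both calculations show no bias when compliance is balanced, and a bias that grows with the imbalance.

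**The case against.** The strongest reply is that the design works against a difference in compliance. Patients are blinded; the sham handpiece matches the real one in look, sound and vibration; there are only four sessions, in weeks when both arms also attend exercises. Setting the pressure by tolerance may keep patients attending rather than drive them away. This stands as an argument about likelihood. A reader might infer that the primary estimate is certain to be biased, and the documents do not support that: they report no compliance figures, and with equal compliance the bias is nil. But balance cannot be known in advance, and the covariate is not needed to estimate the effect of assignment.

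A second reply is that intention to treat only means analysing patients in their allocated arm, and that a covariate moves nobody between arms. That is a fair reading of the term. The objection that survives it concerns the estimand: the adjusted coefficient may not be the effect of assignment.

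Third, the list is introduced as illustrative, and a separate analysis plan may exist. Neither helps, because compliance is named explicitly.

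On scope, a reader might extend the point to every between-group analysis. The text does not support this. No covariates are given for the Cox model of return to work, and compliance is not named for the mixed model of SPADI over 1 year. That mixed model is exploratory and does not replace the primary model. Nor does the text suggest that compliance is coded in the active arm only: the sentence on recording it directly follows the description of the sham.

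**Conclusion.** The defect in the stated plan is clear: the only primary model given, under an intention-to-treat commitment, conditions on a variable observed after randomisation. Whether this causes bias is conditional. Compliance must differ by arm, and it must share causes with SPADI change or lie on the causal path.

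Under the assumed rates the bias runs from 0 to about -4 points, against a target difference of 10. A small imbalance (90 % against 95 %) costs 0.6 to 0.9 points and leaves the type I error close to nominal. The upper end needs both a 25-point gap in compliance and strong selection. The direction also rests on assumption: it favours rESWT only if attendance is lower on rESWT and attenders do better. The standard error takes all 144 patients as analysed and the planning SD of 20.

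Secondary outcomes analysed with the same approach inherit the problem. For return to work this cannot be said.

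**What to change.** Delete compliance with rESWT from the covariate list of the primary model and of the secondary models that use the same approach. State that adjustment is limited to variables measured before randomisation. For drug use and sick leave, this sentence also makes clear that the baseline values are meant.

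If compliance is to be analysed, do so separately and label it supplementary. A complier-average causal effect analysis with randomisation as the instrument is one option, but it is not required.

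The cost is one phrase removed and one sentence added. Data collection and sample size do not change.

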### Outcome measurements and assessment

The patients eligible for inclusion are referred to a physician (EK), who examines all the patients at baseline according to a structured protocol including active and passive range of motion, isometric tests, Hawkins sign, examination of the AC joint and biceps tendon. Ultrasound examination of the affected shoulder is performed the same day. The patients also complete a comprehensive standardised questionnaire including primary and secondary outcome measures, the prognostic demographic and clinical factors including sex, age, duration of symptoms, education, drug use, sick leave status and emotional distress. If an MRI has not been performed within the last 3 months, the patients are also referred for an MRI of the affected shoulder.

Self-reported primary and secondary outcome measures are filled in at each follow-up. At 6 weeks after starting the treatment, the patients fill in a short questionnaire. At 12- and 24 weeks and at 1 year they come to follow-up visits where they have an additional clinical examination, all done by the same blinded physician (EK) Fig 1. At 1 year we also perform ultrasound examination.

The primary outcome measure is the Shoulder Pain and Disability Index (SPADI). The SPADI is a self-assessed, validated shoulder score that consists of 13 questions in two subscales, five about pain and eight about function. We use the original version, with each question scoring previous week’s symptoms on a visual analogue scale (VAS). The total SPADI is calculated from averaging the two subscales, and the total score ranges from 0 to 100 with higher score indicating worse pain and disability [28].

Secondary outcomes are return to work, pain at rest and activity measured on an 11-point Likert type scale, function (ability to take something down from a shelf or to carry a 5-kg shoppingbag) measured on an 11-point Likert type scale, and health related quality of life on EuroQol.

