EuroQol (EQ-5D and EQ-VAS) is a standardised generic instrument for describing and valuing health related quality of life. The EQ-5D comprises five domains that define health in terms of mobility, self-care, usual activities, pain/discomfort and anxiety/depression. Each domain has three response categories; no problem, some or moderate problems, extreme problems. The resulting health state can therefore be defined as a five-digit number by using the response (1–3) from each dimension. Potentially 243 health states can be defined. The five-digit number is then transformed into a number between -0.56 and 1 with 1 representing the best imaginable health state. The EQ-VAS is a self rating of health status on a vertical VAS from 100 (best imaginable health state) at the top to 0 (worst imaginable health state) at the bottom [29].

The patients are instructed not to attend to any other treatment in the study period. We will register on each follow-up visit if they have received any other treatment since the last visit. The use of analgesics is recorded on baseline and on each follow-up visit.

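### Plain Bonferroni for the secondary outcomes is valid, but Holm's step-down version gives the same family-wise error control and never rejects less

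*Protocol article*

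**What the plan says.** The Statistical analysis section fixes the multiplicity method for the secondary outcomes: "Bonferroni correction will be used to correct for multiple testing of secondary outcome". Each outcome gets its own test: "Secondary outcome measures will be assessed with the same approach in separate models", with Cox regression for return to work.

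The outcomes are listed under Outcome measurements and assessment. The list opens "Secondary outcomes are return to work, pain at rest and activity measured on an 11-point Likert type scale", continues with "function (ability to take something down from a shelf or to carry a 5-kg shoppingbag) measured on an 11-point Likert type scale", and ends with health-related quality of life on EuroQol, which has two scores, EQ-5D and EQ-VAS.

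The Sample size section is built on SPADI alone, with "a significance level of 0.05" and a "statistical power of 80" per cent. It promises no power for any secondary outcome.

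**The concern.** Read in the ordinary way, a Bonferroni correction compares every p-value with 0.05 divided by the number of tests. Holm's procedure starts at that same level for the smallest p-value and relaxes it after each rejection. The family-wise guarantee does not weaken and no assumption is added. For the decision whether to reject, single-step Bonferroni therefore gives away some power for nothing.

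The stake is modest. The secondary results help a reader judge whether pain, function, quality of life and work status agree with the SPADI result. If several of them truly differ between groups, plain Bonferroni will leave some non-significant that Holm would have declared.

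**Working it through.** **The plan's own figure.** The document gives no adjusted level, divisor or power for the secondary outcomes, so there is nothing to reproduce on this exact point. The one design figure is 50 per group for SPADI (difference 10, SD 20). With n = 2(z_α + z_β)²(SD/difference)², a one-sided 0.05 test gives 8 × (1.645 + 0.842)² ≈ 49.5, so 50; a two-sided test gives 8 × (1.960 + 0.842)² ≈ 62.8, so 63. The stated figure thus reproduces only one-sided. That is a separate matter and does not affect what follows.

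**Number of tests.** Return to work (1), pain at rest (2), pain on activity (3), shelf item (4), bag item (5), EQ-5D (6), EQ-VAS (7). The count is six if one of the two pairs (function items, EuroQol scores) is merged, and five if both are. The Bonferroni level is 0.05/7 = 0.0071, 0.05/6 = 0.0083 or 0.05/5 = 0.0100.

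**Why Holm dominates.**
1. With seven tests, Holm compares the ordered p-values with 0.0071, 0.0083, 0.0100, 0.0125, 0.0167, 0.0250 and 0.0500, stopping at the first failure.
2. Every p-value at or below 0.0071 passes, because no threshold is below 0.0071. Holm therefore rejects all that Bonferroni rejects.
3. If m₀ nulls are true, the first false rejection must come while at least m₀ hypotheses remain, at a threshold of at most 0.05/m₀. Its probability is at most m₀ × 0.05/m₀ = 0.05, whatever the dependence.
4. The first step is identical in both methods, so both reject at least one hypothesis in exactly the same data sets.

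**Size of the gain.** Assumptions not in the document: seven two-sided tests, equal correlation 0.5, 80% unadjusted power for each real effect, one test per outcome, and return to work treated like the others. The results come from simulation, with 200,000 replicates in the all-seven case. The Bonferroni value can be checked by hand: the mean of z is 1.960 + 0.842 = 2.802, the critical value at 0.0071 is 2.690, and Φ(0.112) ≈ 54.5%.

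| Real effects among seven | Bonferroni | Holm | Gain (points) |
|---|---|---|---|
| 1 | 54.5% | 54.5% | 0.0 |
| 2 | 54.6% | 55.6% | 1.0 |
| 3 | 54.4% | 56.7% | 2.3 |
| 4 | 54.4% | 58.2% | 3.8 |
| 7 | 54.5% | 65.1% | 10.6 |

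Entries are average power per real effect.

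**Sensitivity.**
- Five tests, all real, correlation 0.5: 59.0% to 68.8%.
- Seven real at 60% unadjusted power: 31.6% to 38.9%.
- The planned 72 per group without dropout, effects of 0.5 SD, correlation 0.5: 62% to 73% if all seven are real, 62% to 66% if four, 62% to 63% if two, and no visible change if one. With two real, the chance of at least one true rejection is 77.94% against 77.96%.
- All seven real at 0.3 SD, correlation 0.5: 19% to 23%.

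**Role of correlation.** With no real effects, the two methods have the same family-wise error: 4.9% at correlation 0, 4.1% at 0.5 and 2.6% at 0.8. Holm therefore does not recover the slack that correlation creates. Its gain is present at correlation 0 and has no fixed direction with correlation. In the all-seven, 80% case it falls (about 11.8, 10.6 and 9.3 points at 0, 0.5 and 0.8). With all seven at 0.3 SD and 72 per group it rises (2.1, 4.3 and 5.2 points).

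**The case against.** The strongest reply is that nothing here is wrong. Bonferroni is pre-specified, valid under any dependence, contradicts nothing in the article, and comes with simple simultaneous intervals (with seven tests, each at 1 − 0.05/7 = 99.29%). No power was promised for the secondary outcomes. That stands: the point concerns efficiency.

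A reader might infer that the outcomes are correlated and that Holm exploits this. The documents give no correlations, and Holm uses only the ordered p-values. Recovering the slack due to correlation would need a resampling or joint-distribution method.

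A reader might also take the all-seven case as the expected benefit: average power 55% to 65%, or the chance of rejecting all seven 16% to 41%. That case assumes every secondary null is false. The article does not support this as a planning premise: its Background reports no evidence of benefit in non-calcific tendinosis, and its Discussion cites an early trial in which sham did better. Nor does the protocol make rejecting all seven an objective.

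Finally, a full plan that is not shown may already specify a step-down version. If so, no change is needed. As published, the wording denotes the single-step method.

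**Conclusion.** The point holds as a minor, optional improvement. For testing the secondary outcomes, Holm is never worse than the stated method and sometimes better. Under the stated assumptions the gain in average power per real effect runs from about 0 to 11 points, and to about 13 in the most favourable scenario run (72 per group, seven real effects of 0.5 SD, uncorrelated: 62.2% to 75.4%). It is close to nothing if only one or two outcomes are affected. The ordering of the two methods does not depend on the assumed correlation, power or number of tests; the size of the gain does.

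It should not be read as an error in the plan, as inflation of the error rate, or as a threat to the SPADI conclusion, which lies outside this correction.

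**What to change.** In the Statistical analysis section, replace Bonferroni correction with Holm's step-down Bonferroni procedure for the secondary outcomes, before the group comparison is analysed. It needs only the p-values, so it accommodates the Cox model for return to work alongside the other models.

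The cost is a few words, plus one reporting consequence. Holm has no simple matching simultaneous confidence intervals. If unadjusted 95% intervals are shown, label them as unadjusted and note that one may exclude the null value where Holm does not reject. If matching simultaneous intervals matter more to the investigators than the extra power, keeping Bonferroni is a defensible choice.
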